#### 6.4. Withdrawal of individual subjects

Subjects can leave the study at any time for any reason if they wish to do so without any consequences. The investigator can decide to withdraw a subject from the study for urgent medical reasons.

**6.5. Replacement of individual subjects after withdrawal**

New subjects will replace subjects that are withdrawn from the study.

**6.6. Follow-up of subjects withdrawn from treatment**

Subjects withdrawn from treatment will not be followed-up after eventually handing over responsibilities to medical personnel.

## **7. SAFETY REPORTING**

### **7.1. Section 10 WMO event**

In accordance to section 10, subsection 1, of the WMO, the investigator will inform the subjects and the reviewing accredited METC if anything occurs, on the basis of which it appears that the disadvantages of participation may be significantly greater than was foreseen in the research proposal. The study will be suspended pending further review by the accredited METC, except insofar as suspension would jeopardise the subjects' health. The investigator will take care that all subjects are kept informed.

### **7.2. Adverse and serious adverse events**

Adverse events are defined as any undesirable experience occurring to a subject during the study, whether or not considered related to the experimental intervention. All adverse events reported spontaneously by the subject or observed by the investigator or his staff will be recorded.

A serious adverse event (SAE) is any untoward medical occurrence or effect that at any dose:

- results in death;
- is life threatening (at the time of the event);
- requires hospitalisation or prolongation of existing inpatients' hospitalisation;
- results in persistent or significant disability or incapacity;
- is a congenital anomaly or birth defect;
- is a new event of the trial likely to affect the safety of the subjects, such as an unexpected outcome of an adverse reaction, lack of efficacy of an IMP used for the treatment of a life threatening disease, major safety finding from a newly completed animal study, etc.

All SAEs will be reported through the web portal *ToetsingOnline* to the accredited METC that approved the protocol, within 15 days after the sponsor has first knowledge of the serious adverse reactions.

SAEs that result in death or are life threatening should be reported expedited. The expedited reporting will occur not later than 7 days after the responsible investigator has first knowledge of the adverse reaction. This is for a preliminary report with another 8 days for completion of the report.

**7.3. Follow-up of adverse events**

All adverse events will be followed until they have abated, or until a stable situation has been reached. Depending on the event, follow up may require additional tests or medical procedures as indicated, and/or referral to the general physician or a medical specialist.

## **8. STATISTICAL ANALYSIS**

### **8.1. Descriptive statistics**

Data will be presented as means  $\pm$  standard error of the mean (SEM). Energy expenditure will be expressed as total 36h energy expenditure, as well as for the different components (SMR, DIT and AEE). Substrate oxidation will be calculated as carbohydrate, fat and protein oxidation and as RQ. Total energy and macronutrient intake will be calculated to subsequently calculate energy and macronutrient balance. VAS ratings and POMS and STAI scores will be described. Area under the curve (AUC) and area above the curve (AAC) will be calculated using the trapezoidal method for all the variables described above.

### **8.2. Univariate analysis**

The Statistical Package for the Social Sciences (SPSS) will be used to perform univariate analyses. ANOVA repeated measures will be performed to determine possible differences in energy expenditure and its components, substrate oxidation, *ad libitum* energy intake, energy and macronutrient balance, appetite profiles and mood scores between the four conditions. Multiple linear regression analyses will be performed to determine the independent contribution of gender, age, and factors describing body composition and body fat distribution on the dependent variables. All statistical tests will be two-sided and differences will be considered statistical significant if  $p < .05$ .

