## SUMMARY

**Rationale:** Red pepper might prevent reduction of energy expenditure and elevation of hunger as a result of energy intake restriction.

**Objective:** To investigate the acute effects of capsaicin on energy expenditure, substrate oxidation, appetite profile and *ad libitum* energy intake during negative energy balance.

**Study design:** The study will be conducted in a crossover design with four randomly sequenced conditions. Energy expenditure and substrate oxidation will be continuously monitored for 36h. Appetite profile will be measured hourly. *Ad libitum* energy intake will be measured during the last meal.

**Study population:** Sixteen healthy subjects (8 males and 8 females) with BMI between 20-30 kg/m^2 and aged between 18-50 years will be included in the study. All subjects will be non-smoking, weight stable, dietary unrestrained, and at most moderate alcohol and caffeine consumers. Subject will be free of medication except for oral contraceptives use in women.

**Intervention:** Subjects will stay for each of the four conditions in a respiration chamber for 36h, twice receiving an energy-balanced (100 En%) diet and twice an energy-restricted (75 En%) diet, both with and without added capsaicin (100%control, 75%control, 100%CAPS, 75%CAPS). An *ad libitum* meal will be served at the end of the second day.

**Main study parameters/endpoints:** Energy expenditure, substrate oxidation, appetite profile and *ad libitum* energy intake.

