## 2. OBJECTIVES

The primary objective of this study is to investigate whether the 36h effects of capsaicin in 25% negative energy balance prevent the effects of the negative energy balance on energy expenditure, substrate oxidation, appetite profile and *ad libitum* energy intake compared to 100% energy intake without capsaicin (75%CAPS vs. 100%Control).

Because of the cross-over design of this study, it needs to be assessed whether, and to which extend, 75% energy intake without capsaicin decreases energy expenditure and satiety compared to 100% energy intake without capsaicin (75%Control vs. 100%Control). In this way, this study will assess the effectiveness of capsaicin as bioactive ingredient during negative energy balance.

The primary objective implies that 100% energy intake with capsaicin increases energy expenditure, fat oxidation and satiety compared to 100% energy intake without capsaicin (100%CAPS vs. 100%Control). Previous studies have shown comparable effects of capsaicin supplementation, but different subject groups and supplementation protocols were used. This study needs to determine whether capsaicin supplementation is effective over 36h in this specific study setting.

Negative energy balance causes a shift in substrate oxidation, leading to a higher fat oxidation compared to energy balance conditions. This study will test the hypothesis that the increase in fat oxidation will be larger in the 75% energy intake with capsaicin condition compared with 75% energy intake without capsaicin condition (75%CAPS vs. 75%Control).

Four conditions will be applied in order to completely answer the research questions:

- 100% energy balance without capsaicin (100%Control)
- 75% energy balance without capsaicin (75%Control)
- 100% energy balance with capsaicin (100%CAPS)
- 75% energy balance with capsaicin (75%CAPS)

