### 4.4. Sample size calculation

The primary endpoint of this study is the change in 36h energy expenditure.

For the sample size calculation the following formula was used:

$$N = 2 + (Z_{1-\beta} + Z_{1-\alpha/2})^2 \times \sigma^2 / (\mu_{75\%CAPS} - \mu_{75\%CONTROL})^2$$

Herein the  $\beta$  was set at 0.10, which results from a power of 0.9. Consequently,  $Z_{0.9} = 1.28$ . For the  $\alpha$  a value of 0.05 was chosen, which resulted in  $Z_{0.975} = 1.96$ .

It is hypothesized that the 25 En% restriction CAPS diet will show a relatively larger 36h energy expenditure compared with the 25 En% restriction control diet. A study by Yoshioka et al. showed that a combination of red pepper and caffeine significantly increased 24h energy expenditure compared to a control condition ( $10190 \pm 1550$  vs.  $9870 \pm 1490$ ,  $p < .05$ ) (7). This corresponds to an increase in 24h energy expenditure of 320 kJ/24h. Therefore, the smallest change in 36h energy expenditure ( $\mu_{75\%CAPS} - \mu_{75\%CONTROL}$ ) was set at  $1.5 \times 320 = 480$  kJ/36h. The standard deviation was set at 550 kJ/36h, based on several studies performed in the same setting to measure energy expenditure with a respiration chamber as will be used in the current study (25, 26).

The calculated sample size will be:

$$N = 2 + (1.28 + 1.96)^2 \times 550^2 / 480^2 = 14 \text{ subjects}$$

Taking a drop-out of 10% into account, 16 subjects will be included in the experiment.

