## 6. METHODS

### 6.1. Study parameters/endpoints

#### 6.1.1. Main study parameter/endpoint

The primary endpoint of this study is the change in 36h energy expenditure.

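### The protocol contradicts itself on its primary endpoint and primary contrast, so the 5% error rate used for sizing is not tied to one identifiable test

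*Protocol*

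**What the plan says.** **Endpoint.** Section 6.1.1 states: "The primary endpoint of this study is the change in 36h energy expenditure". Section 4.4 repeats this, and section 6.1.2 lists substrate oxidation, the appetite scales and *ad libitum* intake as secondary. The Summary, however, puts all four under its main study parameters, and its objective likewise covers "energy expenditure, substrate oxidation, appetite profile and *ad libitum* energy intake". The primary objective in section 2 names the same four outcomes.

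**Contrast.** Section 2 says: "Four conditions will be applied in order to completely answer the research questions". It names four pairwise comparisons and attaches the primary objective to 75%CAPS vs 100%Control. The denominator of the formula in section 4.4 is instead the difference between 75%CAPS and 75%Control.

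**Error rule.** In section 4.4, for alpha, "a value of 0.05 was chosen, which resulted in" a normal quantile of 1.96. Beta "was set at 0.10, which results from a power of 0.9". In section 8.2, "All statistical tests will be two-sided and differences will be considered statistical significant" if p < .05. The only comparison of conditions that section names is a repeated-measures ANOVA across the four conditions. It does not say which result is primary.

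**The concern.** A trial sized at 5% two-sided and 90% power makes that promise for one comparison on one outcome. Here the reader cannot tell which one. By sections 4.4 and 6.1.1 it is energy expenditure, and by the Summary and section 2 it is any of four outcomes. By section 2 the contrast is 75%CAPS vs 100%Control, and by section 4.4 it is 75%CAPS vs 75%Control.

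The two contrasts ask different things. The first asks whether restriction with capsaicin matches full intake without it. The second asks whether capsaicin raises expenditure under the same restriction. They can disagree, and the protocol does not say which would decide the trial. A statistical analysis plan cannot follow both versions, so this is not a detail that can simply be left to it.

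**Working it through.** **1. The plan's own figure.** Inputs from section 4.4: 1.28, 1.96, SD 550 kJ/36h ("The standard deviation was set at 550 kJ/36h"), and a difference of 1.5 × 320 = 480 kJ/36h ("This corresponds to an increase in 24h energy expenditure of 320 kJ/24h").

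(1.28 + 1.96)² × 550² / 480² = 13.78, which rounds up to the stated 14. With the printed leading 2 it is 15.78, or 16, so the 14 is reached only without that term. This is a separate matter. What counts here is that the calculation covers one contrast (75%CAPS vs 75%Control) on one endpoint at two-sided .05.

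**2. The sections side by side.**

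| Item | Sections 4.4, 6.1.1, 6.1.2 | Summary and section 2 |
|---|---|---|
| Primary or main outcomes | 1 (36h energy expenditure), others secondary | 4 |
| Contrast | 75%CAPS vs 75%Control (4.4) | 75%CAPS vs 100%Control (section 2) |

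**3. What this does to the error rate.** The protocol does not fix a testing procedure, so each figure below belongs to one reading. Correlations between endpoints are not in the protocol and are assumed.

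*Two direct capsaicin contrasts, unadjusted* (75%CAPS vs 75%Control and 100%CAPS vs 100%Control), with no true capsaicin effect. They share no condition, so treating them as independent:
- one endpoint: 1 − 0.95² = 9.8%
- four independent endpoints: 1 − 0.95⁸ = 33.7%

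*All four named contrasts, unadjusted and without an ANOVA gate*, no true difference anywhere. These share conditions, so the rate was simulated with paired t-tests (60,000 trials per setting, n = 14 and 16):
- one endpoint: about 16%
- four endpoints: 50% at correlation 0, 48% at 0.3, 44% at 0.5, 34% at 0.8, 20% at 0.99

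*Omnibus ANOVA only*, no true difference anywhere:
- one endpoint: about 5%
- any of four endpoints: 6% to 19%, depending on correlation

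*All four contrasts examined only after a significant ANOVA*, no true difference anywhere:
- one endpoint: about 4.5%
- four endpoints: 6% to 17%

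**4. Does the ANOVA gate protect the capsaicin question?** Only if diet has no effect either, and section 2 expects restriction to act. A further simulation (40,000 trials per setting, n = 14 and 16) assumed no capsaicin effect and a diet effect of 1 SD of the paired difference. The ANOVA was significant in over 99% of trials. The chance of at least one false result on the two direct capsaicin contrasts was then about 10% on one endpoint and about a third over four independent endpoints, the same as without a gate.

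**The case against.** Three points on the other side carry weight.

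First, section 8.2 names only a repeated-measures ANOVA and does not say that each pairwise contrast is tested at p < .05. Follow-up tests and multiplicity adjustment are often left to a statistical analysis plan, and none is shown here. This stands. A reader might infer that the plan carries a false-positive rate of 16% to 50%, but the document does not support that. The range requires no true difference anywhere, ungated and unadjusted pairwise tests, and any contrast counting as success. The 50% further requires four uncorrelated endpoints, which is unlikely for energy expenditure and substrate oxidation, since both come from the same gas exchange (sections 6.3.2 and 6.3.3).

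Second, sections 4.4, 6.1.1 and 6.1.2 do set an endpoint hierarchy. A reader might take the Summary to create four co-primary endpoints. It is better read as a conflict with those sections, and the more specific text favours a single primary endpoint. But the primary objective itself names all four outcomes, so the conflict goes beyond a label in the synopsis.

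Third, not every named contrast is a capsaicin claim. 75%Control vs 100%Control checks the effect of restriction, and in 75%CAPS vs 100%Control a significant shortfall would count against capsaicin. This also stands, and is why the two direct contrasts give the more relevant figure.

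None of this settles which contrast is primary. An omnibus test across four conditions cannot answer the pairwise questions in section 2.

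**Conclusion.** The point holds as an internal contradiction. The protocol gives two answers on the primary endpoint and two on the primary contrast, and its single p < .05 rule does not choose between them. The contradiction itself rests on no assumption.

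The size depends on the reading: about 5% for the omnibus ANOVA on energy expenditure alone, and about 10% for the two direct capsaicin contrasts on that endpoint. The latter rises to about a third over four endpoints, an upper figure because it takes them as independent. The 16% and 50% figures reproduce, but they describe the least restrained reading and not a property that the plan fixes. The matter should be corrected because it decides what the trial can conclude.

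**What to change.** - Reword the Summary and section 2 to agree with sections 4.4 and 6.1.1, so that 36h energy expenditure is the only primary endpoint.
- Name one primary contrast, tested at two-sided .05, and use it in sections 2, 4.4, 6.1.1 and 8.2. 75%CAPS vs 75%Control is the natural choice because the trial was sized on it and N stays as it is. The primary objective in section 2 must then be reworded, which is an open change to the stated objective.
- If the sponsor prefers to keep 75%CAPS vs 100%Control, redo the sample size justification for it. Section 4.4 gives no expected difference for that comparison, and a claim that capsaicin prevents a fall would need a criterion for what counts as prevented.
- State in section 8.2 that the other contrasts and endpoints are secondary, reported with 95% confidence intervals and not as the trial's primary answer. Any ordering or adjustment among them can be left to the statistical analysis plan.

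With the sized contrast as primary, the cost is wording only. The downside is that fewer results can be claimed as confirmatory.

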## **9. ETHICAL CONSIDERATIONS**

### **9.1. Regulation statement**

The study will be conducted according to the principles of the Declaration of Helsinki (9th version, October 2008, Seoul) and in accordance with the Dutch version of the Medical Research Involving Human Subjects Act (in Dutch: Wet Medisch-wetenschappelijk Onderzoek met mensen; WMO).

### **9.2. Recruitment and consent**

Subjects from the student population will be recruited by advertisements on notice boards at the Maastricht University. They will be informed about the study by reading the provided written 'subject information'. The researchers will orally check their comprehensiveness. An independent person who's well informed about the study could eventually provide additional information, and subjects will be referred to the CCMO brochure 'General information for research participants' that contains general information about medical-scientific research. After being well-informed subjects will get one week before they have to decide to participate in the study. All subjects will confirm their approval for participation by signing an informed consent form.

### **9.3. Benefits and risks assessment, group relatedness**

This study does not have any benefits for the subjects themselves, but will give possible new knowledge for treatment of obesity. Besides, the study does not include any major risk for the subjects. Anthropometric and body composition measurements, performed within several minutes during the screening, will not be invasive for the subjects. Deuterium dilution has been shown to be a safe method for determining total body water. Subjects have to consume an amount of about 150 mL of water in which a small amount of deuterium is diluted. The taste of the solution is comparable to normal water (28). The completion of screening questionnaires will take about 30 minutes.

Accidental findings during the screening related to health status will be communicated to the concerned subjects, whereafter they can individually undertake further steps.

Although the space in the comfortable designed respiration chamber is limited, it is still possible to move freely. Curtains ensure privacy when needed. The door of the respiration chamber is closed, but in case of emergency it could always be opened from inside to leave the chamber. Safety precautions include a fire alarm and extinguisher, emergency power and lighting, subject registration on a building fire-alert panel and short access to a safe escape route. The registration of oxygen consumption and carbon dioxide production will be performed during an unconscious process. The air in the chamber is continuously regulated.

Besides filling in the questionnaires hourly (which takes about 3 minutes every hour), urine collection over the day and prescribed meal and sleep times, subjects can freely spend their time in the respiration chamber.

Urine sampling will be done in 2L urine bottles added with 10 mL of diluted HCl, which might pose a risk for the subjects. Subjects will be carefully instructed how to handle the bottles to reduce these risks.

Further, there are no risks for the subject in consuming any of the provided meals, because people with certain food allergies are excluded for participation and all meals are composed of regular food items available in normal Dutch supermarkets. The addition of capsaicin (McCormick; origin, India; sample ID EC88746100) to the meals will not form any health risk. Capsaicin is a natural product, which is safe in the given dose that will not exceed the maximum recommended daily dose. The dosage used based upon the maximal dosage given in previous studies (8, 19, 20). The same specific form of red pepper has previously been used in a study of Ludy et al, investigating the effects of red pepper on thermogenesis and appetite (11).

All food items, including capsaicin, are suitable for humans. The commercial available food products will be bought by the researchers and immediately after purchase transported by car to the University. Refrigerated products will be taken in deepfreeze bags. After arrival at the University the refrigerated products will be stored immediately at either a 4°C fridge or a -20°C freezer in the research kitchen from the Department of Human Biology. This research kitchen meets all the criteria for safe and proper use of food items in human clinical studies. Capsaicin will be processed, handled, packaged and transported by McCormick, as described in the HACCP-analysis. After arrival at the University the product will be stored in a locked food depot in the research kitchen. Capsaicin will be stored for a maximum period of one year, which corresponds to the maximum duration of the study and will not exceed the expiration date of the product. A certified dietician controls the storage of the products. Before preparation of the meals the dietician will check the expiration dates of the food items. Expired food items will immediately be removed. All food items will be prepared in the research kitchen from the Department of Human Biology by a certified dietician just before they are offered to the subjects. Fresh food items will be used every day, and food items will be stored for a maximum period of one week. Capsaicin will be weighed and mixed with the tomato juice by the dietician just before it is offered to the subjects. Addition of capsaicin will not largely influence the taste of the tomato juice, although the juice will be slightly spicier. Further information can be found in the guideline 'MEC azM/UM for preparation, delivery and administration of products for human usage in clinical studies'.

**9.4. Compensation for injury**

The investigator has a liability insurance, which is in accordance with article 7, subsection 6 of the WMO.

The sponsor also has an insurance which, is in accordance with the legal requirements in the Netherlands (Article 7 WMO and the Measure regarding Compulsory Insurance for Clinical Research in Humans of 23th June 2003). This insurance provides cover for damage to research subjects through injury or death caused by the study.

€ 450.000,-- (i.e. four hundred and fifty thousand Euro) for death or injury for each subject who participates in the Research;

€ 3.500.000,-- (i.e. three million five hundred thousand Euro) for death or injury for all subjects who participate in the Research;

€ 5.000.000,-- (i.e. five million Euro) for the total damage incurred by the organisation for all damage disclosed by scientific research for the Sponsor as 'verrichter' in the meaning of said Act in each year of insurance coverage.

The insurance applies to the damage that becomes apparent during the study or within 4 years after the end of the study.

